#### 2.8.2 Concealment mechanisms

The randomization is performed by a staff member not involved in any other aspect of the trial. Once a participant is ready to be randomized the randomization staff opens a sealed envelope and reveals the training group. The participant’s intervention group is then shared with a different staff member in charge of the study training. Nobody else involved in the study has access to the randomization envelopes and they do not know any information related to the randomization procedure and sequence.

#### 2.8.3 Implementation

Individuals who provide their consent, fulfill the inclusion criteria, and complete the baseline assessment are randomized. The recruitment coordinator shares the new participant’s initials, sex, and birth date to the randomization staff, who reveals the newly assigned training group to the training coordinator.

### 2.9 Blinding

ACTIONcardioRisk is a double-blinded trial. Research personnel performing the outcome assessments at baseline, 6, and 12 months are blinded to group allocation. Participants are also blinded to the “active” intervention and study hypotheses. To maximize the blinding, all participants are informed that throughout the year everyone will have to do some tablet-based cognitive sessions (without specifying whether they are training sessions or assessments). The training groups were described in such a way that the participants could not identify the types or difference between the training groups. However, it is impossible to objectively know if at some point they found a way to guess the type of interventions available. In case of medical necessity, the participant could be unblinded, and the principal investigator will be contacted to allow the disclosure. No modification of group allocation can be made by participants or study staff during the intervention.

### 2.10 Data collection

The collection of measurements and training data throughout the study is managed by assessors and trainers using online case report forms specifically dedicated to each testing session. Medical data is collected on paper and stored separately from all other study data.

### 2.11 Data management

All physically collected data is stored in locked filing cabinets in the research center. Data from those files is entered electronically immediately after the collection by the same research assistant that receives or collects the data. All electronic data is password protected. All research data uses only the participant ID as a means of identification.

### 2.12 Statistical methods

Data analyses will be blinded to the participants’ intervention arms. All participants randomized will be included in the analyses using an intention to treat method. The variables in the study will be presented using descriptive statistics. The mean, standard deviation, median, minimum, Q1, Q3, and maximum will be analyzed as continuous variables. The number and percentage will be presented for the nominal/ordinal variables. The assumptions of the statistical tests (including normality tests) will be examined, and data transformation or non-parametric analyses may be used as appropriate, according to the guidelines (Tabachnick and Fidell, 2019). The SPSS software and SAS version 9.4 or higher software will be used to conduct the analyses.

The primary outcome will be the changes in cognitive performance (MoCA, processing speed, executive functions, and memory). Computerized cognitive tasks will be analyzed separately. We will perform four linear mixed-effects models analyses (for every cognitive measure) with intervention group as fixed factors and adjustments for relevant covariates. An unstructured covariance structure will be used to model the within-patient errors. The final selection of covariates will include age, sex, and education and any potential relevant demographic variable that show a group difference. These will consider, but not be limited to BMI, stress, mood, genetic risk, medical history, and CVRF. A Bonferroni correction will control for multiple comparisons with a significance level set at *p* < 0.0125. The same statistical model will apply for the brain imaging secondary outcomes: pulsatility, vasoreactivity and autoregulation indices, regional cerebral blood flow, grey matter volume and CSVD lesions (Bonferroni-corrected for number of regions). To inform potential future studies, exploratory analyses will also performed in which we will test if certain variable impact the effectiveness of the intervention on the primary (cognition) or secondary (imaging) variables. Due to the exploratory nature of those analyses, no multiple comparison correction will be made and no *a priori* power analysis is made. The exploratory analyses can include but not be limited to testing the mediating or moderating role of the available medical (including cardiovascular health, cardiovascular risk factors), psychological, and biological markers on the group effect. The mediating and moderating analyses will be performed according to the guidelines published by Hayes (2017).

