### 1.2 Objectives

The goal of this trial is to document the impact of a combined physical and cognitive training intervention on neurocognitive functioning in participants with cardiovascular risk factors, while considering individual factors such as sex and specific alleles and mutations in targeted genes thought to modulate the impact of exercise on cognition and brain functions.

The primary hypothesis will test if the multidomain intervention will show higher cognitive benefits (on global cognition, speed of processing, executive functions, and memory) than the physical exercise training or active control after 12 months of treatment. Secondary objectives will assess if the multidomain intervention will show greater brain imaging benefits (on cerebral autoregulation, cerebral vasoreactivity, cerebral pulsatility, and brain structure) relative to the other two groups. Exploratory objectives will assess if the training improvements are modulated by baseline individual difference factors (like genetic profile, biomarkers, vascular health markers, and psychological markers), but also investigate the potential mediating effects of certain variables that can change over the course of the intervention (e.g., vascular health markers, and psychological markers).

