### 1.3 Trial design

ACTIONcardioRisk is a randomized, double-blind trial of superiority, using an active control group and recruiting physically inactive older adults with cardiovascular risk factors to be allocated to one of three parallel intervention arms: Arm 1—Physical exercise intervention (aerobic and resistance exercises); Arm 2—Multidomain intervention (combined cognitive training with aerobic and resistance exercises); Arm 3—Active control (stretching and toning exercises). The randomization is stratified by sex, with a 1:1:1 training group allocation and it will be done by a staff member uninvolved in this study. The participants’ involvement in the study will be 1 year, with 46 weeks of active training. The participants will be assessed at baseline (T0), 6 months (T1), and 12 months (T2). The testing period will last 2–3 weeks at each timepoint, with three testing sessions per week. During this testing period, no training will be performed. The trial design is illustrated in Figure 1 according to the SPIRIT guidelines (Chan et al., 2013). Please see Table 1 for the World Health Organization trial registration data set.

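### The primary mixed model names group but no visit, group-by-visit or baseline-score term and no 12-month contrast, so on repeated responses its group effect need not be the 12-month benefit in the hypothesis

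*Protocol article*

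**What the plan says.** Section 1.2 (Objectives) states the primary hypothesis: the multidomain arm will show more cognitive benefit "than the physical exercise training or active control after 12 months of treatment". Section 1.3 (Trial design) sets three assessments: "The participants will be assessed at baseline (T0), 6 months (T1), and 12 months (T2").

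Section 2.12 (Statistical methods) defines the endpoint and the model:

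- Endpoint: "The primary outcome will be the changes in cognitive performance (MoCA, processing speed, executive functions, and memory").
- Fixed effects: four linear mixed models, one per measure, "with intervention group as fixed factors and adjustments for relevant covariates".
- Covariance: "An unstructured covariance structure will be used to model the within-patient errors".
- Covariates: "The final selection of covariates will include age, sex, and education and any potential relevant demographic variable that show a group difference". Further candidates are listed as open-ended, and all of them are participant characteristics such as BMI, mood and medical history.
- Error rate: "A Bonferroni correction will control for multiple comparisons with a significance level set at" 0.0125.
- The same model is to be used for the imaging outcomes.

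No section names visit, a group-by-visit interaction, the baseline cognitive score as a covariate, or a contrast at 12 months. Nor does section 2.12 say which visits supply the responses.

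**The concern.** An unstructured within-patient covariance implies several records per participant. A group effect without a group-by-visit term is then held constant over the visits analysed, and its estimate is a covariance-weighted average of the visit-specific group differences. The hypothesis concerns one visit, month 12. The two coincide only when the group difference is the same at every visit included.

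At stake is which quantity the confirmatory test estimates. If the benefit builds over the year, as the article's case for a one-year programme suggests, pooling month 6 with month 12 understates the 12-month effect. The text also leaves more than one primary estimate open, so the choice could be made after the data are seen.

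A second, smaller matter is precision. The baseline score is collected and is normally a strong predictor of follow-up, but it is not a named covariate.

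**Working it through.** **Inputs from the documents.** Section 2.6 gives a difference of 0.425 − 0.239 = 0.186, SD 0.298, standardised effect 0.186/0.298 = 0.624, 42 per arm for 80% power at two-sided 0.05, and 20% attrition. Section 2.12 gives alpha 0.05/4 = 0.0125.

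**Assumptions not in the documents.**
- The effect of 0.186 and the SD of 0.298 refer to the 12-month change.
- The between-visit correlation r is 0.5 to 0.8, with equal variances. Compound symmetry is the main case and AR(1) a check.
- The 6-month group difference is a fraction f of the 12-month difference.

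**The plan's own figure.** A two-group t-test (noncentral t) needs 42 per arm, with power 0.807. Then 42/0.8 = 52.5, rounded up to 53, and 3 × 53 = 159. The stated sample size reproduces, and the point does not depend on it.

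**Reference.** The 12-month change contrast at alpha 0.0125 with 42 per arm has power 0.62. The fall from 0.81 comes from the smaller alpha and is a separate matter.

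**General formula.** With visit covariance V, the generalised least squares estimate of a constant group effect weights the visit-specific differences by w = 1′V⁻¹/(1′V⁻¹1).

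**Reading A: the 6- and 12-month changes are the responses.** Under compound symmetry the weights are 1/2 and 1/2, so the group term keeps (f + 1)/2 of the 12-month effect. The two changes share the baseline and correlate 0.5, so their average has variance (1 + 0.5)/2 = 0.75 times that of one change. The SD is 0.298 × √0.75 = 0.258, whatever r is.

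| 6-month effect (f) | Share kept | Difference estimated | Power at 0.0125 |
|---|---|---|---|
| 0.50 (linear gain) | 75% | 0.140 | 0.47 |
| 0.75 | 87.5% | 0.163 | 0.63 |
| 1.00 (full by 6 months) | 100% | 0.186 | 0.77 |
| 12-month change contrast | 100% | 0.186 | 0.62 |

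Under AR(1) the weights lean towards month 6, from 0.75/0.25 at r = 0.5 to 0.90/0.10 at r = 0.8. With linear gain the share kept is then 0.75 × 0.5 + 0.25 = 62.5%, falling to 0.90 × 0.5 + 0.10 = 55%.

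**Reading B: raw scores at all three visits are the responses.** Under compound symmetry each visit has weight 1/3 and the expected baseline difference is zero, so the term keeps (0 + f + 1)/3: 50% for f = 0.5 and 67% for f = 1. The score variance is 0.298²/(2(1 − r)), and the variance of the three-visit mean is (1 + 2r)/3 times that.

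| r | Power, f = 0.5 | Power, f = 1 |
|---|---|---|
| 0.5 | 0.22 | 0.42 |
| 0.7 | 0.10 | 0.19 |
| 0.8 | 0.06 | 0.11 |

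A simulation with estimated unstructured covariance at r = 0.7 (150 runs, Monte Carlo SE 0.02 to 0.03) agreed. The share kept was 0.76 and 1.04 under reading A, and 0.55 and 0.67 under reading B, for f = 0.5 and f = 1.

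**Reading C: only the 12-month change is the response.** The group term is then the 12-month contrast. Each participant has one record, however, and the stated within-patient covariance has nothing to model.

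**Baseline adjustment.** The variance of a change is 2σ²(1 − r), and that of a 12-month score adjusted for baseline is σ²(1 − r²). The ratio is (1 + r)/2, a reduction of (1 − r)/2: 25% at r = 0.5 and 10% at r = 0.8. Power for the 12-month contrast rises from 0.62 to 0.77 at r = 0.5, 0.71 at r = 0.7 and 0.68 at r = 0.8.

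**The case against.** The model is one sentence in a condensed article, and the plural in its fixed-effects phrase suggests that a term was lost in compression. Visit terms and contrast statements are commonly left to an analysis plan, which is not shown. That would settle the matter if section 2.12 were silent on the model. It is not: it states the fixed effects, covariance, covariates and alpha, and the fixed effects as stated do not match the hypothesis.

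The outcome could also be the 12-month change alone, which would make the group term correct. This cannot be excluded. The same model is applied to MRI outcomes that Table 2 schedules only at baseline and 12 months, so the covariance sentence may be generic. The text does not say so, however, and the cognitive tests are scheduled at all three visits.

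A reader might infer that the primary test is bound to lose most of its power. The documents do not support that. The lowest figures arise only under reading B, which fits an outcome defined as changes least well, and they depend on an assumed correlation. Under reading A power may fall or rise. An early effect is plausible, since section 1.1 cites a benefit of combined training after 6 months, although it also expects longer programmes to do better.

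Finally, an unadjusted change score is valid in a randomised trial. Leaving out the baseline score costs precision and does not cause bias. That objection stands.

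**Conclusion.** The point holds as a mismatch between the stated primary model and the stated primary hypothesis. On the most natural reading, the group term equals the 12-month effect only if the whole effect is present by 6 months. With linear gain it keeps 75% of that effect under compound symmetry, or 55–63% under AR(1).

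The effect on power is not established. Under reading A with compound symmetry it is 0.47, 0.63 or 0.77 for half, three quarters or all of the effect at 6 months, against 0.62 for the 12-month change contrast. Under the less likely raw-score reading the term keeps 50–67% of the effect, with power 0.06 to 0.42 over assumed correlations of 0.5 to 0.8.

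Omitting the baseline score forgoes a 10–25% reduction in variance over the same correlations (power 0.68 to 0.77 with adjustment). All power figures assume 42 per arm, alpha 0.0125 and the sample-size effect taken as a 12-month change. The correlations and build-up profiles are assumptions.

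**What to change.** State in section 2.12, for each of the four cognitive measures:

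- Responses: the 6- and 12-month scores.
- Fixed effects: group, visit (categorical), group-by-visit, baseline score, baseline-by-visit, age, sex and education.
- Covariance: unstructured within participant, as now.
- Primary estimate: the group contrast at 12 months, with the 6-month contrast reported as supportive.

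For MRI outcomes measured only at baseline and 12 months, use the 12-month value adjusted for its baseline value. Imaging outcomes measured at all three visits can take the same form as cognition.

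The cost is analysis wording only. All the values are already scheduled, and neither the sample size nor the visit schedule changes. The wording should be settled before any unblinded comparison of the arms.

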### 2.6 Sample size

A power and sample size analysis was performed by a biostatistician team independent of the study team, based on a previous meta-analysis comparing exercise training alone to combined physical and cognitive intervention on cognition (Zhu et al., 2016). Using an intent-to-treat principle with multiple imputations, a sample size of 42 subjects in each group will have 80% power to detect a group difference in means of −0.186 (the difference between a physical alone training mean of 0.239 and a combined training mean of 0.425, for an effect size of 0.624) assuming that the common standard deviation is 0.298 using a two group *t*-test with a 0.050 two-sided significance level. Taking into account a 20% attrition rate observed in our previous exercise studies, we will thus recruit 53 participants per intervention arm (53 × 3 arms), for a total of 159 participants. For the secondary outcome (neuroimaging), we based our calculation on the 2% increase in hippocampal volume following a 12-month physical exercise training reported by Erickson et al. (2011) (Erickson et al., 2011). Results suggest that 60 participants are needed to observe significant changes post-exercise. Since 2 arms involve exercise training in this study (total 106 participants), the numbers of participants are largely enough.

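### The four primary cognitive outcomes are tested by single-step Bonferroni at 0.0125: valid for four tests, but Holm's step-down keeps the same 5% family-wise error and can add power, once the family of tests is stated

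*Protocol article*

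**What the plan says.** Section 2.12 (Statistical methods) names four primary measures: "The primary outcome will be the changes in cognitive performance (MoCA, processing speed, executive functions, and memory"). Each has its own model: "We will perform four linear mixed-effects models analyses (for every cognitive measure) with intervention group as fixed factors". The correction is then stated: "A Bonferroni correction will control for multiple comparisons with a significance level set at" p < 0.0125. No step-down rule, hierarchy or re-use of alpha is named, so every outcome faces 0.0125 whatever happens on the others. The imaging outcomes get a Bonferroni correction for the number of regions.

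Section 1.2 (Objectives) expects benefit on all four measures: "the multidomain intervention will show higher cognitive benefits (on global cognition, speed of processing, executive functions, and memory"). It names two comparators: "than the physical exercise training or active control after 12 months of treatment".

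Section 2.6 (Sample size) says that "a sample size of 42 subjects in each group will have 80% power", and assumes that "the common standard deviation is 0.298 using a two group *t*-test with a 0.050 two-sided significance level".

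**The concern.** A single-step correction charges every outcome the full price even after others have been shown. Holm orders the p-values and compares the smallest with 0.05/4, the next with 0.05/3, then 0.05/2, then 0.05, and stops at the first failure. The later thresholds are looser, and the family-wise error bound is still 5%. The difference is largest when several outcomes truly benefit, which is what section 1.2 predicts.

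At stake are the second to fourth outcomes. A real effect on, say, memory could be reported as not significant although the same data support it at the same family-wise error rate.

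**Working it through.** **1. The plan's own figures reproduce.**
- Threshold: 0.05/4 = 0.0125.
- Effect size: 0.186/0.298 = 0.624.
- Sample size: the two-sided t-test at 0.05 needs 42 per arm (power 80.7%). With 20% attrition, 42/0.80 = 52.5, so 53 per arm.
- At 0.0125, the same 42 per arm give 62.1% power for one outcome.

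**2. Holm keeps the 5% error rate.** Let m0 of the hypotheses be true nulls. Holm makes a false rejection only if the smallest p-value among those nulls is at or below 0.05/m0. By the Bonferroni inequality the chance of that is at most m0 × 0.05/m0 = 0.05, whatever the correlation.

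**3. Holm loses no rejection.** Its thresholds over four tests are 0.0125, 0.0167, 0.025 and 0.05, none below 0.0125. Any p-value under 0.0125 therefore passes. The first threshold is the same in both methods, so the chance of at least one rejection is also the same.

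**4. Size of the gain, by simulation.** From section 2.6: 42 per arm, d = 0.624, two-sample t-tests. Assumed, because the article does not give them: a common correlation of 0.3 to 0.7 between outcomes, the number of outcomes with a real effect, and the smaller effect sizes.

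| Real effects | Bonferroni, power per affected outcome | Holm |
|---|---|---|
| Four at 0.624 | 62% | 70–72% |
| Three at 0.624 | 62% | 67–68% |
| Two at 0.624 | 62% | 64–65% |
| One at 0.624 | 62% | no change |
| Four at 0.4 | 24% | about 29% |
| Four at 0.3 | 12.5% | 14–15.5% |

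With four effects of 0.624, the chance of establishing all four rises from 24–39% to 47–59%. With no real effect, the family-wise error is the same for both methods and at most 4.7% over this range of correlation. A separate simulation with normal test statistics gave the same pattern at slightly higher levels (64% to 72–74% per outcome with four effects). There Holm's family-wise error, when some effects were real, was at most 4.5%.

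**5. The result depends on the family.** The figures above assume one test per outcome. Section 1.2 implies two contrasts per outcome, so the family may be 4 × 2 = 8 tests.
- Eight tests at 0.0125 each give a bound of 8 × 0.0125 = 0.10.
- If Holm were run over four outcomes with both contrasts read at each step, the last outcome could be tested at 0.05 on each of two contrasts. That is looser than the present rule.
- Holm over all eight tests starts at 0.05/8 = 0.00625 and holds 5%. That start is stricter than 0.0125 because the family is larger. Over the same eight tests, Holm still rejects everything Bonferroni rejects.

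**The case against.** The strongest reply is that nothing here is wrong. Bonferroni at 0.0125 is valid, pre-specified and consistent with four measures and four models. That stands: a reader might infer that the plan fails to control type I error over its four tests, and the article does not support that.

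The headline gain is also a best case. Section 2.6 gives one effect size for cognition as a whole and does not give 0.624 for each of the four measures. Section 1.2 predicts benefit on all four but not equal benefit. A gain of 8 to 10 points should therefore not be read as the expected one. The percentages also come from two-arm t-tests on 42 per arm, whereas section 2.12 plans covariate-adjusted mixed models on everyone randomised. They are illustrative.

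Holm is not free either. Bonferroni has matching 98.75% intervals, and Holm has no simple equivalent. If Bonferroni-level intervals are shown beside Holm p-values, an outcome that Holm rejects may have a displayed interval that includes zero. Keeping tests and intervals coherent is a legitimate reason to stay with Bonferroni.

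Finally, the step-down thresholds hold 5% only if the family is fixed first, and section 2.12 does not say which contrast each 0.0125 applies to. This stands too and shapes the fix.

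What the reply does not remove is the dominance result: over the same family Holm cannot lose a rejection and may gain some, whatever the effect sizes and correlation.

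**Conclusion.** An optional but worthwhile improvement in efficiency; the validity of the plan is unaffected. Under the stated assumptions the gain in power per outcome runs from nothing (one real effect) through 2 to 5 points (two or three effects of 0.624, or four of 0.3 to 0.4) to about 8 to 10 points (four effects of 0.624). The dominance and the 5% bound need none of those assumptions, only a fixed family.

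Two further inferences are tempting and unsupported. First, Holm does not repair the mismatch between sizing at 0.05 and testing at 0.0125: 80% power at 0.0125 would need 59 per arm, or 59/0.80 = 73.75, so 74 after attrition. Second, the gain for the imaging outcomes cannot be stated, because the article gives no number of regions, effects or correlations for them.

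**What to change.** In section 2.12, before unblinding:

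1. State the family of primary tests: either one named contrast per outcome (four tests) or both contrasts of section 1.2 on every outcome (eight tests).
2. Replace single-step Bonferroni at 0.0125 with Holm's step-down procedure at a family-wise two-sided alpha of 0.05 over that whole family, and report Holm-adjusted p-values.
3. Say which intervals will be shown. If they are Bonferroni-level intervals, note that one may include zero for an outcome that Holm rejects.
4. Optionally, use Holm in place of the region-wise Bonferroni for imaging.

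The cost is a few sentences and less simple simultaneous intervals. No extra participants or alpha are needed. The family must be settled before the procedure is changed, and both before results are seen.
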